## Introduction

1

Chronic prostatitis/chronic pelvic pain syndrome (CP/CPPS) is a common disorder with 4 domain manifestations: urogenital pain, lower urinary tract symptoms, psychological issues, and sexual dysfunction.^[1]^ Men of all ages and races may experience prostatitis, with a worldwide prevalence of 2% to 10%,^[2]^ while the prevalence is 15% to 16% in Asia, Europe, and North America.^[3]^ More than 90% of patients with symptomatic prostatitis have CP/CPPS.^[4]^ The first-line treatments for CP/CPPS include antibiotics, α-adrenergic antagonists, and simple analgesics.^[5]^ However, due to the multifactorial nature of this syndrome, no single therapeutic option is adequate and multimodal therapies are needed.^[6,7]^

Currently, there are many management approaches for CP/CPPS.^[8]^ According to previous studies, acupuncture has shown promise for the amelioration of CP/CPPS symptoms, particularly for relieving pain.^[9–12]^ The National Institutes of Health (NIH) Chronic Prostatitis Symptom Index (CPSI)^[13]^ is a valid and easily self-administered outcome measure for men with chronic prostatitis. Our previous pilot study^[14]^ showed that after 8 weeks of treatment, acupuncture was associated with a clinically significant decrease in the NIH-CPSI total score. However, in recent studies the change from baseline of the NIH-CPSI after acupuncture treatment has ranged widely,^[15–21]^ and higher than the minimal clinically important difference of the NIH-CPSI is 4 points.^[22,23]^ The results of these studies have been highly variable.

The primary presentation of CP/CPPS is urological pain,^[4]^ and pain is a predominant topic of research in acupuncture.^[24]^ Studies have shown that acupuncture has an immediate pain-relieving effect.^[25]^ The range of results of previous studies for the efficacy of acupuncture treatment in CP/CPPS may be due to differences in timepoints, places of assessment, and especially the subjective scales used for assessment.

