### Outcome measurement

2.5

The 3 coprimary outcomes are the change from baseline in total NIH-CPSI score measured respectively by the 3 assessment modes after the 4-week treatment.^[13]^ The NIH-CPSI has a total possible score of 43; higher scores indicate more severe symptoms. The 9 items of this scale are stratified into 3 domains as follows: pain/discomfort (location/type, frequency and severity, 0–21 points); urinary symptoms (10 points); and quality of life (0–12 points). The minimal clinically important difference of the NIH-CPSI is 4 points.^[4]^ The 3 modes of assessment are as follows: Mode 1, the scale is recorded at the hospital within 10 minutes after the twelfth (last) treatment of the 4-week treatment period, in the company of the outcome assessors; Mode 2, the scale is recorded the same day, but not at the hospital; and Mode 3, the scale is recorded at the hospital 1 to 3 days after the last acupuncture session. The outcome assessors will be responsible for calling the participants by telephone to remind them to fill the scale after leaving the hospital, and recording the accurate time for filling the scale.

The 3 key secondary outcomes are the 3 modes of assessment of the changes from baseline of the NIH-CPSI total score in the acupuncture group.

The secondary outcomes of this study are the changes from baseline of subscale scores of the NIH-CPSI, and the International Prostate Symptom Score (IPSS). The IPSS (Hong Kong Chinese version 2) is a valid, reliable, and sensitive measure to assess Chinese males, with 7 questions concerning urinary symptoms and 1 question concerning quality of life.^[32]^ The total possible IPSS score is 35 (asymptomatic to very symptomatic). Symptoms evaluated by the IPSS are categorized as mild (0–7), moderate (8–19), or severe (20–35).

The proportions of participants in each response category of the Global Response Assessment (GRA) will be assessed. The GRA comprises 7 response categories: markedly worsened, moderately worsened, slightly worsened, no change, slightly improved, moderately improved, and markedly improved.

The participants’ expectations regarding acupuncture will be measured at baseline. Participants will answer 2 questions: “In general, do you believe acupuncture is effective for treating the illness?”; and “Do you think acupuncture will be helpful to improve your CP/CPPS symptoms?” Participants will choose “Unclear,” “Yes,” or “No” as the answer.

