In addition, during the fourth week of the study period (sessions 11 or 12) participants will be asked to answer the following question within 5 minutes after treatment: “Do you think you have received traditional acupuncture in the past weeks?” The participants will be able to choose one of the following options as the answer: “Unclear,” “Yes,” or “No.”

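### The arm-guess question may fall inside the Mode 1 window after session 12, so its position relative to the three coprimary assessments is neither fixed nor the same for all participants

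*Protocol article*

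**What the plan says.** Both timings are in the Protocol article, section 2.5 (Outcome measurement).

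- **Arm-guess question.** It is put in week 4, timed as follows: "sessions 11 or 12) participants will be asked to answer the following question within 5 minutes after treatment". The wording is "Do you think you have received traditional acupuncture in the past weeks", with Unclear, Yes and No as the permitted answers.
- **Mode 1.** "Mode 1, the scale is recorded at the hospital within 10 minutes after the twelfth (last) treatment of the 4-week treatment period", with the outcome assessors present.
- **Modes 2 and 3.** Mode 2 is filled in on the same day away from the hospital. Mode 3 is filled in at the hospital 1 to 3 days after the last session.
- **Status of the modes.** "The 3 coprimary outcomes are the change from baseline in total NIH-CPSI score measured respectively by the 3 assessment modes". The key secondary outcomes set the three modes against each other within the acupuncture group.

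The Introduction describes the NIH-CPSI thus: it "is a valid and easily self-administered outcome measure for men with chronic prostatitis". Section 2.2 lists participants among the blinded parties. Section 2.7 frames the efficacy hypothesis as superiority on one or more modes.

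**The concern.** The endpoint is the participant's own report. Asking him whether he had traditional acupuncture, minutes before he scores his symptoms, brings his belief about his treatment to mind just as he answers. If beliefs differ between arms, the effect of being asked need not cancel in the between-arm comparison. Beliefs could plausibly differ: sections 2.4.1 and 2.4.2 describe deep needling with manipulation against shallow needling with thinner needles and no manipulation.

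Two analyses are exposed. The first is the Mode 1 efficacy test, which matters because superiority on a single mode satisfies the hypothesis. The second is the comparison of modes. The trial exists to learn whether assessments that differ by minutes, place and company give different answers, and the Discussion itself says situational influences need to be considered. A belief question close to one mode and further from the others is such an influence, and the plan introduces it without holding it constant.

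**Working it through.** **Inputs** (Protocol article). Question: 0–5 minutes after session 11 or session 12 (section 2.5). Mode 1: 0–10 minutes after session 12 (section 2.5). Sample size: difference 4, SD 4.5, two-sided alpha 0.05, 90% power, 28 per group, 6% loss, 60 in total (section 2.7).

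**1. The plan's own figure.** A two-sample t-test with these inputs needs 27.6, so 28 per group, and power at 28 is 0.904. Then 56 / 0.94 = 59.6, which rounds up to 60. The stated sample size reproduces, and this point does not affect it.

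**2. The two windows.** At session 12 the interval 0–5 minutes is wholly contained in 0–10 minutes. If the question is put at session 12, any Mode 1 form started after minute 5 must follow it. A form started earlier may come before or after it.

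**3. Sequences.** I read the article as having each participant complete all three modes.

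| When the question is put | Sequence | Position relative to the modes |
|---|---|---|
| Session 12, question first | Question, Mode 1, Mode 2, Mode 3 | Immediately before Mode 1, further from Modes 2 and 3 |
| Session 12, Mode 1 first | Mode 1, question, Mode 2, Mode 3 | Mode 1 unprompted, Modes 2 and 3 prompted |
| Session 11 | Question, session 12, Mode 1, Mode 2, Mode 3 | Before all three, next to none |

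The stated windows permit all three rows, so participants can be spread over them. Neither session 12 row treats the modes alike.

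**4. Where a shift would enter.** Let a and s be the mean change in the Mode 1 score caused by being asked, in the acupuncture and sham arms. The bias in the Mode 1 efficacy estimate is a − s. If only a fraction f in each arm is asked just before Mode 1, it is f × (a − s). The mode comparison is made within the acupuncture arm, so its bias is the Mode 1 shift minus the shift in the other mode, in that arm alone. It does not require beliefs to differ between arms.

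**5. Illustration only.** The documents give no value for a or s. On the planning figures, SE = 4.5 × √(2/28) = 1.20. With no true effect and a differential shift b, an unadjusted two-sided 5% test rejects with probability 1 − Φ(1.96 − b/SE) + Φ(−1.96 − b/SE).

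| Assumed b (points) | Rejection rate |
|---|---|
| 0 | 5% |
| 0.5 | 7% |
| 1 | 13% |
| 1.5 | 24% |
| 2 | 38% |

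These rates concern Mode 1 on its own. They take no account of the hierarchical testing procedure, whose steps are in a supplement not shown.

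**The case against.** The best reply is that nothing in the article says the question comes first. Mode 1 could be completed before it, or the question could be put at session 11, so the direct priming sequence needs two choices that the article does not make. Form order usually sits in a case report form or visit manual, and the schedule figure is not shown. Unclear is an allowed answer, so nobody is forced to commit to a guess. Participants also hold beliefs whether or not they are asked, and those beliefs bear on all three modes. Only the extra effect of being asked belongs here, and no figure for it exists.

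Most of that stands. A reader might infer that Mode 1 is bound to be biased, or that the bias favours acupuncture. The text supports neither reading: priming is permitted but not certain, and its direction cannot be derived. Nor can a between-arm gap in guesses be used to size the effect on the mode comparison, which is made within one arm.

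What does not stand is that this is only an omitted form order. Both windows are stated, they overlap, and two sessions are allowed. A manual that fixed the order at session 12 would still leave the question placed unevenly across the modes, as the sequence table shows.

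**Conclusion.** The point holds as a scheduling weakness. The stated windows allow a belief question right beside a self-reported coprimary assessment, and they let its position vary between participants and across the modes under comparison. It may prime Mode 1 and may be confounded with the mode comparison.

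Its size is unknown. The 7% to 38% range rests entirely on assumed differential shifts of 0.5 to 2 points, on SD 4.5 with 28 per group, and on an unadjusted test. It shows sensitivity and is not an estimate. The point is worth correcting because the exposure is avoidable at almost no cost, and because the planned data would give no clean way to separate the effect of being asked from the belief itself. It is no reason to doubt the sample size.

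**What to change.** Put the question at one time point for every participant, not next to the Mode 1 scale.

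- **Preferred:** ask it after the Mode 3 form is completed, at the hospital visit already planned 1 to 3 days after the last session. It then follows all three coprimary assessments and cannot influence any of them. Cost: the 5-minute window is dropped and there is a short recall delay.
- **Otherwise:** ask everyone at session 11 and delete the session 12 option. The question then stands in the same position for all three modes, with a full session in between. Cost: it precedes all three outcomes, so priming is made more distant but not excluded, and anyone who misses session 11 has no answer.

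Either is a one-line change to section 2.5 and the schedule, with no new visit, staff or recalculation.

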### Safety assessment

2.6

Adverse events related to acupuncture treatment and the rate of incidence will be carefully recorded in the case report forms. Adverse events include severe pain, broken needle, fainting, local hematoma, localized infection, and postacupuncture discomfort. Severe pain will be reported by Visual Analogue Scale (≥7 points). Postacupuncture discomfort may be nausea, vomiting, palpitation, dizziness, headache, anorexia, and insomnia during treatment period. The severity and duration of postacupuncture discomfort will also be recorded.

In addition, adverse events that are irrelevant to the treatment will be recorded during the study period. In the event of any serious adverse event, researchers will report the details to the principal investigator (ZL) and the Medical Ethics Committee within 24 hours.

### Calculation of sample size and statistical analyses

2.7

We hypothesize that acupuncture will be more effective than sham acupuncture, according to at least one assessment mode, at week 4 after treatment. Based on the results of a previous electroacupuncture study,^[14]^ we estimated that 28 patients were required in each group to provide 90% power to detect a difference of 4 in the NIH-CPSI total score, with a standard deviation of 4.5 at a 2-sided alpha level of 0.05. Accounting for a 6% loss during follow-up, we calculated that we would need to enroll 60 patients.

All efficacy analyses were performed on an intention-to-treat population, and included all patients who were randomly assigned, regardless of whether they received treatment. Safety analyses were defined as all patients who received at least one treatment session. We analyzed the change from baseline in the NIH-CPSI total score by fitting a general linear model, with the baseline value as a covariate, and treatment as a fixed effect. The same approach was used for the 3 key secondary outcomes and the change from baseline in the IPSS score. Categorical variables were compared using Fisher exact test or the Wilcoxon rank-sum test, as appropriate.

To account for multiplicity to test the 3 primary hypotheses and the 3 secondary hypotheses, a hierarchical procedure for multiple testing was used to control the overall type I error rate. For further details, see Table 2, Supplemental Content, which illustrates the Hierarchical procedure for multiple testing, in 6 steps.

Missing data on the primary outcome were assumed due to random occurrence and were imputed using the multiple imputation method. All statistical analyses were performed using Statistics Analysis System version 9.4 software (SAS Institute) with 2-sided tests at a significance level of 0.05.

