### Objective of this study

1.1

This study will determine the efficacy of acupuncture treatment for patients with CP/CPPS after 4 weeks of treatment, and evaluate 3 modes of assessment of efficacy.

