### Study design

2.1

This trial is designed as a randomized sham-controlled multicenter trial with 2 parallel groups. It will be conducted at the following 5 hospitals: Guang’anmen Hospital, West China Hospital of Sichuan University, Yantai Hospital of Traditional Chinese Medicine, Hengyang Hospital Affiliated to Hunan University of Chinese Medicine, and The First Hospital of Hunan University of Chinese Medicine. The development of the study protocol conformed to the guidelines of the Standard Protocol Items: Recommendations for Interventional Trials (SPIRIT)^[26]^ and the Standards for Reporting Interventions in Clinical Trials of Acupuncture (STRICTA).^[27]^ This study will be conducted in accordance with the principles of the Declaration of Helsinki^[28]^ and has been approved by the Ethics Committee of Guang’anmen Hospital (Ethical number 2018-098-KY, see Table 1, Supplemental Content, which illustrates the ethical documentation) and the Research Ethics Committee of the aforementioned hospitals.

This trial has been registered at www.clinicaltrials.gov (NCT 03641807).

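### The model stated for the three key secondary outcomes, which are confined to the acupuncture arm, has treatment as its only factor and so compares no assessment mode with another

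*Protocol article*

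**What the plan says.** Section 1.1 gives two aims: the efficacy of acupuncture after 4 weeks, and to "evaluate 3 modes of assessment of efficacy". Section 2.1 describes a "randomized sham-controlled multicenter trial with 2 parallel groups".

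Section 2.5 defines two families on the same scale. The primary family is between arms: "The 3 coprimary outcomes are the change from baseline in total NIH-CPSI score measured respectively by the 3 assessment modes after the 4-week treatment". The key secondary family lies within one arm: "The 3 key secondary outcomes are the 3 modes of assessment of the changes from baseline of the NIH-CPSI total score in the acupuncture group".

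Section 2.7 gives the primary model as "fitting a general linear model, with the baseline value as a covariate, and treatment as a fixed effect". It extends this model to the second family: "The same approach was used for the 3 key secondary outcomes and the change from baseline in the IPSS score". Both families enter formal testing: "To account for multiplicity to test the 3 primary hypotheses and the 3 secondary hypotheses, a hierarchical procedure for multiple testing was used". The six steps of that procedure are in Table 2 of the supplement, which was not available for this review.

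**The concern.** The outcome definition and the model do not fit together. The definition removes the sham arm; the model's only factor is the contrast between acupuncture and sham. Nothing in the model refers to mode, which is what the second aim is about.

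The Discussion (section 3) explains why that aim matters: scores taken immediately after treatment, or with an assessor present, may overstate the effect. If the test for the three key secondary hypotheses is undefined, someone must choose it later, and half of the six-hypothesis hierarchy is not prespecified in substance.

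**Working it through.** **Inputs.** Difference 4, SD 4.5, two-sided alpha 0.05, power 90%, 28 per group, 6% loss, 60 enrolled (all section 2.7); 1:1 allocation (section 2.2). The within-patient correlation r between modes is not in the article and is assumed to be 0.5 to 0.9.

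**1. The plan's own figure.** Normal approximation: n = 2 × (1.960 + 1.282)² × 4.5² / 4² = 26.6, so 27 per group. The two-sample t-test needs 27.6, so 28, with power 0.904. Then 56 / 0.94 = 59.6, so 60. The stated sample size reproduces. It concerns the between-arm comparison only.

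**2. The stated model in the acupuncture arm.** For patient i with baseline b and treatment indicator T:

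change_i = β0 + β1·b_i + β2·T_i

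Every patient has T = 1, so this is change_i = (β0 + β2) + β1·b_i. Only the sum β0 + β2 can be estimated. A numerical check with 30 patients in the arm agrees: the design matrix (intercept, baseline, treatment) has 3 columns and rank 2.

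**3. Other ways to read the sentence.**

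| Reading | Rank / columns | What is tested |
|---|---|---|
| Acupuncture arm, one mode at a time | 2 / 3 | Adjusted mean change in that mode; no treatment effect, no mode contrast |
| Acupuncture arm, three modes stacked, no mode term | 2 / 3 | Adjusted mean change averaged over modes; no mode contrast |
| Both arms, one mode at a time | 3 / 3 | Acupuncture against sham in that mode, which is the co-primary analysis again |
| Acupuncture arm, stacked, mode added | 4 / 4 | Mode contrasts estimable |

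Only the last row compares modes, and the article does not state that model. Because all three scores come from the same patient within about 3 days of the last session, it also needs a within-patient covariance.

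**4. Illustration of why pairing matters.** Assume 28 patients analysed and SD 4.5 in each mode.

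- Pairing ignored: SE = 4.5 × √(2/28) = 1.20.
- Paired: SE = 4.5 × √(2(1 − r)/28).

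| Assumed r | Paired SE | 1.20 / paired SE |
|---|---|---|
| 0.5 | 0.85 | 1.4 |
| 0.8 | 0.54 | 2.2 |
| 0.9 | 0.38 | 3.2 |

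Ignoring the pairing would make the test conservative. At r = 0.5 the true two-sided type I error would be 2 × [1 − Φ(1.96 × 1.203 / 0.850)] = 0.0056 instead of 0.05, and lower still at higher r.

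**The case against.** The strongest reply is that the supplement's hierarchy table may set out the hypotheses, and that an article condenses the full protocol. That would excuse silence. But the article is not silent: it names a model for these very outcomes, and the table is described as showing the testing order. A table of steps would not undo the model statement.

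Three stronger readings are tempting, and the objection succeeds against each.

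- A reader might infer that the model cannot be fitted at all. Software would typically drop the aliased term and fit intercept plus baseline. The exact statement is that the treatment effect is not estimable and no mode is compared.
- A reader might infer that the plan pools the three records as independent and so uses a wrong standard error. Section 2.7 describes no pooling, and a general linear model can carry repeated measures. The figures in step 4 of the working are therefore illustrative. The loss would fall on small mode differences: for a difference of 4 points, the minimal clinically important difference in section 2.5, power with pairing ignored would still be about 97% at r = 0.5.
- A reader might take the three hypotheses to be the pairwise mode contrasts. This is plausible given the aim and the restriction to one arm, but it is not stated. Three within-arm changes, or a treatment effect that differs by mode, are also possible. The model in section 2.7 supplies neither a pairwise contrast nor an interaction, and three within-arm changes would not evaluate one mode against another.

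**Conclusion.** Wrong as written, with high confidence for the mismatch itself, which rests on the wording of sections 2.5 and 2.7 and needs no assumed number. The stated model cannot answer the mode question, which is one of two stated aims and, on the most natural reading, the subject of three of the six hypotheses in the hierarchy. That the hypotheses are mode contrasts is an inference from section 1.1 and the single-arm definition.

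The standard errors (0.85 to 0.38 paired, 1.20 unpaired) depend on the assumed correlation, on 28 analysed patients and on an equal SD of 4.5 in each mode. They show what the choice of analysis is worth, not an error the plan has committed. The three co-primary between-arm analyses are estimable as stated, and 28 per group and 60 in total stand.

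**What to change.** 1. Remove the key secondary outcomes from the sentence in section 2.7 that extends the primary model. Keep that model for the co-primary outcomes and the IPSS.
2. State the three key secondary hypotheses explicitly as mode contrasts, consistent with section 1.1 and the supplement's hierarchy table.
3. Analyse them within patient in the acupuncture arm: a repeated-measures or mixed model with mode as factor, baseline NIH-CPSI as covariate and unstructured covariance across the three modes, or paired differences.
4. If the intended question is whether the acupuncture-sham effect differs by mode, say so, and use both arms in the same repeated-measures model with a treatment-by-mode interaction. Section 2.5 would then have to drop the restriction to the acupuncture group.

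The cost is one paragraph of wording. No new data or patients are needed. The change should be made before unblinding.
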